# Physical Activity With Tailored mHealth Support for Individuals With Intellectual Disabilities: Protocol for a Randomized Controlled Trial

**DOI:** 10.2196/19213

**Published:** 2020-06-29

**Keywords:** intellectual disability, physical activity, technology, mHealth, mobile phone, goal attainment, social support, self-efficacy

## Abstract

**Background:**

Individuals with intellectual disabilities (IDs) have lower levels of physical activity (PA) and greater barriers for participation in fitness activities compared with members of the general population. As increased PA has positive effects on cardiovascular and psychosocial health, it is exceedingly important to identify effective interventions for use in everyday settings. Mobile health (mHealth) methods such as motion sensor games (exergames) and smartphone reminders for PA have been explored and found to be promising in individuals with IDs.

**Objective:**

The purpose of this study is to examine the effectiveness of an individually tailored PA program with motivational mHealth support on daily levels of PA in youth and adults with IDs.

**Methods:**

The trial uses a randomized controlled design comprising 30 intervention participants and 30 control group participants, aged 16 to 60 years, with sedentary lifestyles or low PA levels. While the controls will receive standard care, the intervention aims to increase the level of PA, measured as steps per day, as the primary outcome. Secondary outcome variables are body mass index, blood pressure, physical performance, social support for PA, self-efficacy in a PA setting, behavior problems, and goal attainment. The intervention involves the delivery of tailored mHealth support, using smartphones or tablets to create structure with focus on the communicative abilities of individual participants. Rewards and feedback are provided in order to motivate individuals to increase participation in PA. Participants in the intervention group, their close relatives, and care staff will be invited to participate in a preintervention goal-setting meeting, where goal attainment scaling will be used to select the participants’ PA goals for the intervention period. All participants will be assessed at baseline, at 3 months, and at 6 months.

**Results:**

Enrollment was planned to start in April 2020 but will be delayed due to the pandemic situation. The main contribution of this paper is a detailed plan to run our study, which will produce new knowledge about tailored mHealth to support PA in individuals with intellectual disabilities.

**Conclusions:**

We expect the new intervention to perform better than standard care in terms of improved PA, improved self-efficacy, and social support for activities. Technology offers new opportunities to promote healthy behaviors. The results of the study will determine the effectiveness and sustainability of a tailored mHealth support intervention to increase PA in youth and adults with IDs.

**Trial Registration:**

ClinicalTrials.gov NCT04079439; https://clinicaltrials.gov/ct2/show/NCT04079439

**International Registered Report Identifier (IRRID):**

PRR1-10.2196/19213

## Introduction

The prevalence of intellectual disabilities (IDs) is estimated to be 1% of the world’s population [1,2]. Compared with the general population, individuals with IDs have worse health and lower levels of activity [3-5], and they have greater barriers for participating in fitness activities [6] and accessing health care services [7,8].

### Physical Activity Guidelines

The World Health Organization (WHO) guidelines for physical activity (PA) state that typical adults should spend a minimum of 150 minutes per week engaged in moderate-intensity PA or 75 minutes engaged in vigorous-intensity PA [9]. One systematic review found that only 9% of individuals with IDs met the WHO´s minimum PA guidelines [4]. Norwegian guidelines are in line with the international guidelines and recommend 150 minutes of moderate- to vigorous-intensity PA per week for adults [10] and 60 minutes per day for children and youths [11]. As high PA is a determinant of health and increased activity has positive effects on cardiovascular and psychosocial health, identifying effective interventions for use in everyday settings is exceedingly important.

### Physical Activity Interventions

Some well-designed studies have not been able to demonstrate improved levels of PA in intervention groups of individuals with IDs after the intervention period has ended. One theory-based randomized controlled study of adults with all types of IDs did not find any significant increases in levels of PA (steps per day) using a walking program [12]. Furthermore, the results of a cluster-randomized study of older adults in the Netherlands showed marginal effects and substantial missing data, despite being well prepared with a published protocol and using day-activity centers for the intervention [13]. Past controlled studies on the effects of PA interventions on individuals with IDs have primarily included adults with mild to moderate IDs, and effect sizes have been small [5,14]. Some studies have reported improved effects on physical fitness indicators such as balance and muscle strength [15], psychological well-being [16], perception of social competence [17], and work routines [14] after increasing levels of PA. One recent study included individuals with severe or profound IDs in a technology-aided program for promotion of PA and found positive results in energy expenditure and independent engagement in light to moderate PA [18], but with a small number of participants. Findings from previous studies indicate that a more flexible approach [19], greater use of theory in intervention design, stronger research design (as there are few randomized controlled studies), and better translation of interventions to community-based settings [20] are needed. Future studies could also have an ecological approach, where the interplay between individual, interpersonal, and environmental factors are considered [1,21]. Motivational issues have been challenging, particularly for approaches that aim for sustainable effects [17], and should be considered when designing future PA interventions.

### Mobile Health Interventions

Mobile health (mHealth) provides a wide range of possibilities for monitoring and motivating individuals in the self-management of chronic illnesses [22-24]. Motion sensor games (exergames) have been explored and have been found to be promising in individuals with IDs [25]. For these solutions to move out of the lab and into actual use, they need to first meet users’ needs [26]. The mobile platform is ubiquitous, and the touch interface has proven to have a low level of cognitive demand and could be used to improve adherence to PA [27]. At present, few mobile apps have incorporated games strategies, such as goal setting or rewards, to increase PA in individuals with various disabilities [28]. To our knowledge, there has been only 1 preliminary report (letter) of a randomized controlled trial using smartphone support to increase motivation for PA in youth and adults with IDs [29].

Methods that could facilitate the development of individualized mHealth support solutions include tailoring, individual goal setting [30], and adjusting communication to meet the specific needs of individuals with IDs [31]. Studies on motivation for PA in the IDs population have shown that predictability with routine and familiarity, communication of purpose, and enjoyable and social activities promote motivation and participation [21,32]. Family and care staff involvement will be central, and we expect the study’s implementation in a natural setting to enhance the effect [33]. We also expect the systematic use of mHealth with rewards and gamification to be beneficial. In Norway, many individuals with IDs have a smartphone or a tablet that they can use for tailored PA interventions. However, this use has not been tested previously. We expect a motivational app for smartphones and tablets to promote adherence to PA in individuals with IDs. According to the *World Report on Disability*, health promotion efforts targeting this population can improve lifestyle behaviors [34]. The report states that these individuals have the right to be included in all PA programs. Thereby, the present study aims to examine the effectiveness of an individually tailored PA program with motivational mHealth support on everyday levels of PA in youth and adults with IDs, targeting individual, contextual, and interactional factors of PA participation [21]. In addition to higher levels of PA, we expect improvements in psychological health, self-efficacy in activities [32], and social support for physical activity participation [35].

## Methods

### Design

The current study has a randomized controlled clinical design with assessments at baseline, 3 months, and 6 months. Participants will receive either the tailored mHealth-supported PA program or standard care with access to the mHealth support system once the trial is completed. Family and care staff will be involved in the program for support and follow-up.

### Participants

A total of 60 participants will be recruited into the trial through health care and other related organizations in the municipality of Tromsø in northern Norway. Information about the study will be delivered at meeting places, such as day and activity centers. If the number of included participants is insufficient, more municipalities in Northern Norway will be included, or a multicenter approach will be considered.

### Inclusion and Exclusion Criteria

Individuals will be included if they have a sedentary lifestyle [1] or a low level of PA, determined with the question, “In how much of your leisure time have you been physically active in the last year?” [8]. The question has 4 response categories and has been used in population-based studies of the general population [36] and in European health indicator studies of individuals with IDs [8]. Individuals with a sedentary lifestyle (eg, primarily engaged in reading, watching television, or other mainly sedentary activities) and a low level of PA (eg, engaged in walking or other light PA for less than 4 hours a week) will be included in the study. Other inclusion criteria will be as follows: (1) diagnosis of ID (mild, moderate, severe, or profound), (2) aged between 16 and 60 years, (3) ability to participate in the intervention, (4) ability to walk with or without support, and (5) able to provide written informed consent or written informed consent can be obtained from a representative. Prior to enrollment, all participants will be screened for readiness, and, if necessary, medical clearance will be obtained. The Physical Activity Readiness Questionnaire [37] will be used for this purpose. Exclusion criteria will be as follows: (1) medical contraindications for participation in programs with increased exercise as advised by the primary care or ID specialist physician, (2) high level of physical activity, and (3) inability to provide written informed consent and written informed consent cannot be obtained from a representative.

### Ethics

This study has been approved by the Regional Committee for Medical and Health Research Ethics in northern Norway (number 2016/1770). The protocol has been registered at ClinicalTrials.gov under the identifier NCT04079439. The project adheres to the Consolidated Standards of Reporting Trials guidelines. Written informed consent will be obtained from each participant, their legal representative, or both prior to inclusion in the study and baseline assessment. If the participant has impaired capability to consent, consent will be sought from the nearest relative or guardian as well as from the individual with IDs, or as representative consent. Ethical issues will be continuously considered. Any adverse events will be recorded.

### Randomization

Participants will be randomized with a computer program to either the PA intervention with mHealth support group or the standard care control group.

#### Intervention Group

This randomized controlled trial is part of our project to develop a tailored mHealth support system that promotes PA in individuals with IDs [38]. In previous parts of the project, we conducted a qualitative study on motivation for participation in PA for individuals with IDs [21], held workshops and collaborated with mHealth developers, and performed usability tests. This process is illustrated in Figure 1.

Findings from the qualitative study, discussions in workshops, and creative meetings among developers and researchers showed that many individuals with IDs experience difficulties participating in PA because of individual, interactional, and contextual factors. Some of these factors include individual difficulties in initiating activities; preferences for fun and social activities; and lack of social support, availability of activities, resources and preparation, predictability, and collaboration in activities. After examination of these findings, a prototype of an app was created and presented in one of the workshops. The feedback was promising, and development of the mHealth support system continued. The main emphasis in the app is individually chosen activities, tailored communication, predictability, use of rewards, and involvement of support persons. Activities will be chosen during a goal attainment meeting (using goal attainment scaling) [39] with the individual with ID and a support person (usually a family member or health care provider). Goal attainment is widely used as an outcome measure within rehabilitation medicine [39] and has been used in studies with individuals with IDs [40]. The research group is familiar with the use of goalsetting processes in previous studies with individuals with IDs. The final intervention will consist of an advanced activity planner based on the platform for the app Active Leisure (Smart Cognition AS). Actiplan features and tracks daily physical activities. The app offers different interface options (symbols only, easy-to-read text, plain text, and read aloud). See Figure 2 for examples. The activity planner will mostly be used by the individual with ID and a support person (caregiver or health care provider). After completing an activity, a simple reward is available (eg, a smiling face or sharing a picture with other users of the app). The use of tailored communication [41] is available through personalization, including the use of the individual’s first name in the activity planner, individually chosen activities, adjusted communication (eg, symbols, easy-to-read text, or plain text), preparation and planning, and feedback. Rewards and positive feedback after activities have been performed are expected to increase motivation, and thereby lead to higher levels of PA.

In addition, 3 individual exercise apps have been developed as potential alternatives that can be added to Actiplan: (1) an exergame or game-inspired app that promotes outdoor PA; (2) an ergometer bike or outdoor bike placed inside the home, with a mounted screen showing a video or other visually interesting features; and (3) a game-inspired, avatar-based health platform for monitoring PA and motivating users to increase their PA levels [38].

To explore the participants’ expectations and experiences of the intervention and the mHealth support, a qualitative pilot study recruiting 10 of the first participants in the intervention group will be performed.

**Figure 1 figure1:**
[figure not shown]
Development process of the electronic health support component of the study.

**Figure 2 figure2:**
[figure not shown]
Interface options of the Actiplan app: symbols only, easy-to-read text, or plain text. The app also has read-aloud capabilities.

#### Control Group

Participants in the control group will be administered the assessments at baseline, 3 months, and 6 months, and otherwise continue with their standard everyday activities during the study period. They will be invited to use the mHealth support system at the end of the 6-month intervention period.

### Data Collection

Data will be collected at baseline, 3 months, and 6 months, as seen in Figure 3. Baseline data will include baseline PA activity level and will be collected before randomization. Follow-up data will be collected regardless of the participant’s compliance with the study protocol. Participants and assessors will not be blinded. Background data on the participants will be collected at baseline and will include age, gender, educational level, marital status, living condition, employment status, educational status, job-related or day center activities, leisure time activities, smoking habits, level of ID (ie, mild, moderate, severe, or profound), genetic diagnosis, gross motor function classification [42,43], communication level [44], medical history/readiness for the PA intervention, and use of medication. In addition, we will ask questions about barriers for participation in physical activities.

**Figure 3 figure3:**
[figure not shown]
Consolidated Standards of Reporting Trials flow diagram of the study. mHealth: mobile health.

### Outcome Measures

#### Primary Outcome

The primary outcome of this study will be objectively measured PA, as assessed by steps per day measured with a wrist-worn commercial accelerometer (Fitbit Versa; Fitbit Inc). The device will assess level of PA and sedentary time [45]. The watch will be covered (neutral screen) during baseline and follow-up assessments in both the intervention and control groups. Screen neutrality is achieved by running a custom app on the watch that disables all buttons and prevents screen feedback (except showing current time). This app cannot be disabled by the participant. Level of PA will be measured for 7 days at each assessment, with a minimum of 3 consecutive days of measurement because previous research has shown that 3 days of PA can predict the weekly level of PA [14,46]. Many of the commercial fitness trackers have been validated for use in research [47], including devices from Fitbit Inc [48,49].

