##### Physical Activity

The secondary PA outcome is the number of minutes of moderate PA per day, measured with the commercial accelerometer.

In addition, the International Physical Activity Questionnaire-Short Form, adapted to measure PA using proxy respondents, will be used [53]. The International Physical Activity Questionnaire-Short Form is a 7-item questionnaire that assesses PA in the past 7 days at 4 intensity levels: (1) vigorous-intensity activity, such as aerobics, (2) moderate-intensity activity, such as leisure cycling, (3) walking, and (4) sitting.

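### The two device outcomes, steps and moderate-only minutes, can under-represent gains from cycling or vigorous activity, both of which the intervention allows

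*Protocol article*

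**What the plan says.** The Objective in the abstract is the "effectiveness of an individually tailored PA program with motivational mHealth support on daily levels of PA in youth and adults with IDs". That is activity in general, not walking.

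Under Intervention Group, the article describes the app this way: "The main emphasis in the app is individually chosen activities, tailored communication, predictability, use of rewards, and involvement of support persons". It adds that "3 individual exercise apps have been developed as potential alternatives that can be added to Actiplan", and the second of these is "an ergometer bike or outdoor bike placed inside the home, with a mounted screen showing a video". The bike is therefore stationary and optional. The number of participants expected to use it is not given.

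Under Primary Outcome, the endpoint is "objectively measured PA, as assessed by steps per day measured with a wrist-worn commercial accelerometer". The same section says that the device also assesses level of PA and sedentary time.

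Under Secondary Outcomes, Physical Activity, the article states: "The secondary PA outcome is the number of minutes of moderate PA per day, measured with the commercial accelerometer". The Secondary Outcomes text and Table 1 also refer to moderate activity alone. Two further secondary outcomes bear on PA:
- a proxy version of the International Physical Activity Questionnaire-Short Form, with separate vigorous, moderate, walking and sitting levels and leisure cycling as its example of moderate activity;
- goal attainment scaling on up to 3 PA goals.

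Under Physical Activity Guidelines, the article says that Norwegian guidelines "recommend 150 minutes of moderate- to vigorous-intensity PA per week for adults".

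**The concern.** The objective outcomes are narrower than the activity the intervention is meant to produce, in two separate ways.

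1. **Steps and pedalling.** A participant can choose a cycling goal, meet it on a bike the trial offers, and show little or no change in steps. The article does not say how cycling enters the device data. Any such loss falls only on gains in the intervention arm, so it pulls the primary comparison toward no difference.
2. **Moderate minutes only.** As written, a vigorous minute contributes nothing to the secondary device outcome. A participant who replaces moderate minutes with vigorous ones would lose minutes on it.

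At stake are some power on the primary outcome and the reading of a null. If steps do not differ, the listed device outcomes alone could not separate no increase in PA from an increase of a kind they do not count.

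**Working it through.** **Inputs from the article (Sample Size).** Effect size 0.8, power 80%, significance level 0.05 (two-sided assumed; sidedness is not stated). The effect corresponds to about 2000 steps per day, so the implied SD is 2000 / 0.8 = 2500. Stated minimum: 25 per group, 50 in total. Planned: 30 per group, to allow for dropout.

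**Reproducing the plan's figure.** n per arm = 2 × (1.960 + 0.842)² / 0.8² = 24.5, rounded up to 25, or 50 in total. This matches. A t-test calculation gives 25.5, so 26 per arm. The sample-size arithmetic is sound.

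**Assumption not in the article.** Let f be the share of the intended step gain that is lost because the activity produces no steps. The article gives no value for f, so a range is shown. The mean gain becomes 2000 × (1 − f) and the effect size becomes d = 0.8 × (1 − f). Power is for a two-sided two-sample t-test with noncentrality d × √(n/2).

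| f | Mean gain (steps) | d | Power, 30 per arm | Power, 25 per arm |
|---|---|---|---|---|
| 0 | 2000 | 0.80 | 86% | 79% |
| 10% | 1800 | 0.72 | 78% | 70% |
| 20% | 1600 | 0.64 | 68% | 60% |
| 30% | 1400 | 0.56 | 57% | 49% |

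The normal approximation gives 87%, 80%, 70% and 58% at 30 per arm, which agrees within about 2 points. By the same approximation, the arm size needed for 80% power is 31, 39 and 51 at f = 10%, 20% and 30%. If the loss comes from a fraction f of the arm gaining no steps while the rest gain 2000, the spread within the intervention arm also grows. The approximate power at 30 per arm is then 79%, 68% and 56%, a further 1 to 3 points lower.

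**The moderate-only outcome, from the text alone.** The World Health Organization guideline, as the article reports it, accepts 75 vigorous minutes per week in place of 150 moderate ones. That values a vigorous minute at 150 / 75 = 2 moderate minutes. The secondary outcome values it at zero. The Norwegian adult guideline that the article cites also counts both intensities.

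**The case against.** The other side has a good deal in its favour.

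- **Other outcomes cover these gains.** A reader might infer that cycling or vigorous gains would be scored as none by the trial. The documents do not support that. The questionnaire has a vigorous level and names leisure cycling, and goal attainment is scored. What remains is that neither is an objective measure: the questionnaire is answered by proxy, the goal scale is completed by the researcher, and participants and assessors are not blinded.
- **Cycling might register as moderate minutes.** The article's own questionnaire classes leisure cycling as moderate, so the existing device outcome could in principle pick it up. Whether a wrist device does so is not stated. For the same reason, adding vigorous minutes from that device does not cure missed pedalling. The two gaps need separate remedies.
- **The power range is assumed.** A reader might take the table to show that the trial is underpowered. It does not. The bike is optional, a participant who cycles may also have a walking goal, and the 2000-step figure is stated for the intervention group, so it may already allow for people who gain few steps. If it does, nothing further is lost.
- **The shift from moderate to vigorous may be rare.** Entry is limited to people who are sedentary or have low PA, so few may have many moderate minutes to lose. This weakens any claim that the outcome will move the wrong way, but it does not justify leaving vigorous minutes out.
- **Steps are an explicit choice.** The abstract says that PA is measured as steps per day, and the trial is powered on steps. This is a fair reason to keep steps as primary. Ranking the secondary outcomes and fixing how a null is read can be left to the full protocol or SAP.

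**Conclusion.** The point holds in a limited form. The article's objective is daily PA by individually chosen means that may include stationary cycling, while its device outcomes are steps and moderate minutes. Gains from cycling or vigorous activity can therefore be under-represented in the objective outcomes, though not in the full outcome set.

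That steps register little or no pedalling follows from what a step is; the article neither says so nor quantifies it. The loss of vigorous minutes follows directly from the outcome as worded. The effect on power is unknown because uptake of the bike is not stated. The range of 78% to 57% at 30 per arm, for losses of 10% to 30%, shows only how sensitive the design would be. It is not an estimate, and there is no error in the stated sample size. This is a cheap improvement to the outcome set and no reason to replace the primary outcome.

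**What to change.** In Secondary Outcomes, Table 1 and the Physical Activity subsection, replace minutes of moderate PA with minutes of moderate-to-vigorous PA per day from the same device, keeping moderate minutes as a reported component.

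Because this does not ensure that cycling is detected, add one field at the goal meeting recording whether each chosen activity is step-based. Report the step result beside the share of step-based activities.

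The primary outcome, device and sample size stay as they are. The cost is that the secondary outcome is no longer purely moderate intensity, and there is one more item to record at a meeting already planned. The article reports that enrolment had not started, so both changes could be fixed before any data exist. Optionally, the full protocol or SAP could rank the new outcome first among the secondaries and state in advance how a null step result will be read alongside it and the questionnaire.
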